### Cost effectiveness acceptability curves and net benefit

A cost effectiveness acceptability curve will be constructed to express the probability that the cost per extra unit of outcome gained from within the trial (y-axis) is cost effective as a function of the decision-maker's ceiling cost effectiveness ratio (λ) (x-axis)[51]. Net benefit will be determined when λ is £30 000. For the within-trial analysis we will use cost per error avoided.

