**Figure 1 F1:**
[figure not shown]
**decision-analytic model of intervention to reduce preventable drug related morbidity arising from prescribing errors in general practice**.

For the purposes of the within trial analysis of cost per error avoided we will examine the differences in costs of the pharmacist-based intervention compared with simple feedback, in the context of error rate reduction.

For the modelling analysis of cost per quality adjusted life year (QALY) gained, we will examine the differences in overall NHS costs, in the context of QALYs gained.

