### Within trial analysis of outcomes

Outcomes used in the within-trial analysis of cost per error avoided will be number of prescribing errors in each treatment arm.

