### Incremental cost-effectiveness ratios (ICERs)

Incremental cost effectiveness ratios will be calculated for the trial-based analyses and sensitivity analyses.

The effectiveness measure for the calculation of incremental cost effectiveness ratio will be cost per unit of outcome. For the within-trial analysis we will use errors. If the lower cost intervention is also associated with better outcomes than the more costly comparator, this will be treated as efficient. In this scenario, incremental ratios would not be calculated for this intervention, since its use would lead to both net savings and greater benefits. Incremental cost effectiveness ratios will be calculated if the higher cost intervention is associated with better outcomes. The incremental ratios will be calculated as:

Statistical analysis is not appropriate to test the robustness of ICERs. It is not possible to generate 95% confidence intervals around ICERs because the ratio of two distributions does not necessarily have a finite mean, or therefore, a finite variance[50]. Therefore, generation of a bootstrap estimate of the ICER sampling distribution to identify the magnitude of uncertainty around the ICERs is required. Bootstrapping with replacement will be employed, utilising MS Excel^®^, using a minimum of 1000 iterations to obtain 2.5% and 97.5% percentiles of the ICER distribution.

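### The £30 000 net-benefit ceiling has no stated unit and stands in the within-trial section, where it would value each avoided error at £30 000

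*Protocol article*

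**What the plan says.** The protocol article plans two economic analyses with different outcome units.

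- **Within-trial analysis.** The outcome, under Within trial analysis of outcomes, "will be number of prescribing errors in each treatment arm". The section on incremental cost-effectiveness ratios (ICERs) agrees: "For the within-trial analysis we will use errors".
- **Modelling analysis.** The text after Figure 1 introduces the other unit: "For the modelling analysis of cost per quality adjusted life year (QALY) gained". The section Modelling analysis of outcomes adds that utility weights will come from published literature.

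The section Cost effectiveness acceptability curves and net benefit describes a curve for "the probability that the cost per extra unit of outcome gained from within the trial (y-axis) is cost effective", drawn against the decision-maker's ceiling ratio λ. It then fixes one value and names the within-trial unit: "Net benefit will be determined when λ is £30 000. For the within-trial analysis we will use cost per error avoided". Nowhere does the article tie £30 000 to a QALY, give a separate ceiling per error avoided, or justify £30 000 as the value of an error.

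**The concern.** Net benefit is λ times the effect, minus the incremental cost. It has a meaning only when λ is expressed per unit of that effect. Here the only outcome named alongside λ is the error avoided. An analyst who follows the section literally will therefore multiply errors avoided by £30 000. A missed renal-function check would be priced the same as a contraindicated prescription, and each would carry a value so large that the intervention's cost hardly counts.

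At stake is one reported result, the within-trial net benefit, which readers may take as the summary of value for money. A figure that is positive mainly because of the unit attached to λ could be quoted as evidence of cost-effectiveness.

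**Working it through.** **Inputs.** Error rates, cluster sizes and intraclass correlations (ICCs) come from Table 2. The 36 practices per arm come from the Discussion, and λ = £30 000 from the net-benefit section. Incremental cost per practice is not given; I assume £1,000 to £20,000.

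**Reproducing Table 2.** Patients per arm by the two-proportion formula (pooled variance, two-sided 5%, 80% power, no continuity correction) are 1191, 3733 and 312. The design effect 1 + (m − 1) × ICC is 1.671, 3.878 and 1.990. Practices in total are 2 × ceil(n × design effect / m):

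- Peptic ulcer: 2 × ceil(1191 × 1.671 / 63) = 64
- Asthma: 2 × ceil(3733 × 3.878 / 439) = 66
- ACE inhibitor or loop diuretic: 2 × ceil(312 × 1.990 / 105) = 12

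All three match Table 2, so its rates and cluster sizes are a sound basis for the planned effect. I use the asthma ICC printed in the table, 0.00657. The text below the table prints 0.010657, which would need about 98 practices.

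**Planned errors avoided per practice**, m × (control rate − intervention rate):

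| Outcome | Calculation | Errors avoided |
|---|---|---|
| Peptic ulcer, NSAID | 63 × (0.0513 − 0.0288) | 1.42 |
| Asthma, beta-blocker | 439 × (0.0169 − 0.0095) | 3.25 |
| Aged 75 or over, ACE inhibitor or loop diuretic | 105 × (0.1762 − 0.0990) | 8.11 |
| Total | | 12.77 |

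**Value at £30 000 per error.** 12.77 × £30 000 is about £383,000 per practice. If prescribing errors means outcomes 1 and 2 only, 4.67 × £30 000 is about £140,000.

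**Break-even**, cost / λ:

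- £1,000 / £30 000 = 0.03 errors per practice; 0.033 / 12.77 = 0.3% of the planned effect
- £20,000 / £30 000 = 0.67 errors per practice; 0.667 / 12.77 = 5.2% of the planned effect

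**ICER at the planned effect.** £1,000 / 12.77 = £78 and £20,000 / 12.77 = £1,566 per error avoided. The ceiling is about 19 to 380 times these figures.

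**Approximate probability of cost-effectiveness.** The variance of errors avoided per practice is the sum over outcomes of m × design effect × [p_c(1 − p_c) + p_i(1 − p_i)] / 36 = 0.224 + 1.231 + 1.360 = 2.815, so the standard error is 1.678. This treats the three outcomes as independent and the cost as known. With f the fraction of the planned effect achieved, the probability is Φ[(12.77f − cost/λ) / 1.678]:

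| Effect achieved | λ = £30 000, cost £1,000 to £20,000 | λ = £1,000, cost £5,000 |
|---|---|---|
| Full | 1.00 | 1.00 |
| Half | 1.00 | 0.80 |
| One quarter | 0.97 to 0.93 | 0.14 |
| One tenth | 0.77 to 0.64 | 0.01 |
| None | 0.49 to 0.35 | 0.00 |
| Harm, 20% of planned size | 0.06 to 0.03 | 0.00 |

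At £30 000 a twentyfold change in cost barely moves the probability once the effect reaches a quarter of plan. At £1,000 per error, cost decides the answer.

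**The case against.** The best defence is that £30 000 was meant for the cost-per-QALY model. On this view the sentence after it, about cost per error avoided, sets the within-trial analysis apart. That reading is possible, and the article never says outright that an avoided error is worth £30 000. But it does not say the opposite either: the section is framed around the within-trial outcome and λ has no unit. The wording needs correcting under either reading.

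Several stronger inferences are tempting, and the article does not support them.

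- *The result is favourable whatever the data show.* It is not. With no effect, expected net benefit is minus the cost; with harm it is clearly negative.
- *The second objective goes untested.* That objective is cost per error avoided, which the ICER answers without any λ. The curve also runs across λ, so lower ceilings remain visible.
- *The effect is a raw count that ignores denominators.* The outcome section does speak of a number of errors, but the text after Figure 1 refers to reduction in error rates. This is loose wording; the estimator can be left to a fuller plan.
- *The uncertainty method contradicts itself.* The plan rejects conventional intervals for the ICER and then bootstraps "to obtain 2.5% and 97.5% percentiles of the ICER distribution". Percentiles exist even where a ratio has no finite mean or variance, so there is no contradiction. How replicates with negative ratios are handled is not stated.
- *Intervals will be too narrow because patients are resampled.* The resampling unit is not stated, and the cost analysis elsewhere allows for clustering.

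**Conclusion.** The point holds, limited to the single within-trial net-benefit figure. With λ at £30 000 per error, that figure would be favourable for almost any appreciable reduction in errors, almost whatever the intervention costs. Break-even is 0.03 to 0.67 errors per practice against a planned 12.8.

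The size rests on three assumptions: the Table 2 rates and cluster sizes, a sum over the three primary outcomes only (the economic analysis also covers outcomes 5, 7 and 8, for which no planned effect is given), and a cost of £1,000 to £20,000 per practice. A higher cost weakens the statement. At £50,000, break-even rises to 1.67 errors per practice (13% of plan), and one tenth of the planned effect would no longer suffice. The clinical analyses, the ICER and the rest of the acceptability curve are untouched.

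**What to change.** In the section on acceptability curves and net benefit:

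1. State the unit of λ.
2. Confine £30 000 to the cost-per-QALY model.
3. For the within-trial analysis, report net benefit and the acceptability curve over a stated range of values per error avoided, or at a separately justified ceiling, with no £30 000 point.

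Two optional additions: report intervals for net benefit from a bootstrap that resamples whole practices, alongside the ICER percentiles; and align the number-of-errors wording under Within trial analysis of outcomes with the error-rate wording after Figure 1.

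The required change costs only wording. The article says that analysis had not been undertaken at submission, so the change can be made without knowledge of the results. The optional bootstrap needs a little more programming.

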### Sensitivity analysis

Sensitivity analysis is required to assess the level of uncertainty in the data collected within the trial and subsequent internal robustness of the results.

The key aspect to be investigated in this analysis will be the impact of:

• size of practice

• alternative models of service delivery.

#### Format of tables for publishing the main trial results and within trial economic analysis

The format of tables for publishing the main trial results and within trial economic analysis is shown in Appendix 2 (see additional file 2).

#### Qualitative study

The qualitative data will be subjected to thematic analysis with the aid of NVivo^® ^software. Actively searching for disconfirming data and regular detailed discussions amongst the qualitative sub-group, and periodic discussions with the wider multi-disciplinary steering group will help ensure the rigour of the analysis.

### Trial Management Group

A Trial Management Group has met of a quarterly basis throughout the study to help ensure that all trial activities are organised according to the protocol and within the timescales set out in the original application for funding.

### Trial Steering Committee

The Trial Steering Committee (TSC) will monitor and supervise the trial and comment on any proposed amendments' to the protocol. The Trial Steering Committee is headed by [name]. [name] and [name] are the other external members of the committee. The TSC and has agreed to operate within the framework suggested in the *MRC Guidelines for good clinical practice in clinical trials *[15].

### Data Monitoring and Ethics Committee (DMEC)

The DMEC is headed by [name]. Other external members of the committee are [name] and [name]. The trial statistician will report to the DMEC, which will be responsible for reviewing the data from the trial. The DMEC has agreed to operate within the framework suggested in the *MRC Guidelines for good clinical practice in clinical trials *[15].

#### Ethical aspects

The clinical trial will be conducted according to the Helsinki Declaration[52], the Good Clinical Practice Guidelines[53] and NHS Research Governance requirements.

Patients agreeing for the study team to access their clinical records have provided written informed consent in a form designed for such purpose. The patient may refuse to continue participating in the study at any time after providing his/her consent.

The information generated by the study will be confidential and limited to the purposes stipulated in the protocol.

The study has been approved by Nottingham 2 Research Ethics Committee (Reference: 05/Q2404/26). All staff involved in data collection will have approval from the appropriate local NHS research and development offices.

#### Study timeline

Trial start: 1 April 2006

Start of baseline data collection and interventions in general practices: August 2006

End of interventions in general practices: February 2008

End of 12 month follow-up data collection: April 2009

Start of data analysis: May 2009

Planned study end date: 30 September 2009

Duration: 3.5 years

## Discussion

At the time of submission of this article, 72 general practices had been recruited (36 in each arm of the trial) and the interventions had been completed.

In keeping with findings from our pilot studies, we have been able to recruit general practices without too much difficulty. It is likely that our success in recruitment relates to the attention to detail we put into developing a feasible intervention that was seen to be relevant to general practices, although we will find out more about whether this was the case from our qualitative study. In addition, we put considerable effort into our recruitment strategy including pre-publicising the trial, sending documentation to general practices about the trial and following up on this to arrange visits to practices where the study was explained in more detail.

Baseline data extraction was undertaken smoothly and successfully and provided the information needed for practices to consider acting on patients with potentially hazardous prescribing and medicines management. In particular, data extraction for our pre-specified primary outcome measures appears to have worked successfully in all general practices recruited to the study. Nevertheless, we have encountered some difficulties with the secondary outcome measures, as described above. Some of these problems could have been avoided with better foresight on behalf of the research team. For example, had we been aware that some general practices kept a separate record of INR results, and did not keep these on their main clinical computer systems, we could have excluded such practices from our recruitment. Similarly, if we had realised that it would not be possible to extract dosage instructions for general practices using the TPP computer system, we could have excluded practices using this computer system (we did pilot our outcome measures using the TPP computer system and went ahead with recruiting practices because we erroneously believed that was a solution to the problem). For outcome measure nine, which focused on dosage instructions for methotrexate, a national policy change that occurred during the course of our study has meant that we will be unable to collect useful follow-up data on this outcome measure for any of the practices we have recruited. This is because the introduction of a forcing function to GP computer systems, which does not allow for anything but weekly dosing, does not appear as a line of dosing text that can be picked up by MIQUEST software. It is unfortunate that our study will not be able to demonstrate the impact of this important safety initiative, although it is likely that the introduction of this computerised safety feature will have brought about improvements in both arms of the trial.

At the time of submitting this protocol, analysis of quantitative data had not been undertaken.

## Abbreviations

ACE: Angiotensin converting enzyme (inhibitor); CHD: Coronary heart disease; CTU: Clinical Trials Unit; DMEC: Data Monitoring and Ethics Committee; GP: General practitioner (or family practitioner); ICC: Intraclass correlation coefficient; ICER: Incremental cost effectiveness ratios; INR: International normalised ratio; IT: Information technology; MRC: Medical Research Council; NHS: The UK National Health Service; NPSA: National Patient Safety Agency; NSAIDs: non-steroidal anti-inflammatory drugs; PCT: Primary Care Trust; PPI: proton pump inhibitor; TPP: The Phoenix Partnership (the name of a GP computer system); TSC: Trial Steering Committee.

